# Effectiveness of robot-assisted training added to conventional rehabilitation in patients with humeral fracture early after surgical treatment: protocol of a randomised, controlled, multicentre trial

**DOI:** 10.1186/s13063-017-2274-z

**Published:** 2017-12-06

**Keywords:** Robot-assisted rehabilitation, Humeral fracture, Randomised controlled study

## Abstract

**Background:**

The incidence of proximal humeral fractures increases with age. The functional recovery of the upper arm after such fractures is slow, and results are often disappointing. Treatment is associated with long immobilisation periods. Evidence-based exercise guidelines are missing. Loss of muscle mass as well as reduced range of motion and motor performance are common consequences. These losses could be partly counteracted by training interventions using robot-assisted arm support of the affected arm derived from neurorehabilitation. Thus, shorter immobilisation could be reached. Thus far, this approach has been tested in only a few small studies. The aim of the present study is to examine whether assistive robotic training augmenting conventional occupational and physical therapy can improve functional shoulder outcomes.

**Methods/design:**

Patients aged between 35 and 66 years with proximal humeral fracture and surgical treatment will be recruited at three different clinics in Germany and randomised into an intervention group and a control group. Participants will be assessed before randomisation and followed after completing an intervention period of 3 weeks and additionally after 3, 6 and 12 months. The baseline assessment will include cognition (Short Orientation-Memory-Concentration Test); level of pain in the affected arm; ability to work; gait speed (10-m walk); disability of the arm, shoulder and hand (Disabilities of the Arm, Shoulder and Hand Outcome Measure [DASH]); range of motion of the affected arm (goniometer measurement); visual acuity; and motor function of orthopaedic patients (Wolf Motor Function Test–Orthopaedic version [WMFT-O]). Clinical follow-up directly after the intervention will include assessment of disability of the arm, shoulder and hand (DASH) as well as range of motion and motor function (WMFT-O). The primary outcome parameter will be the DASH, and the secondary outcome parameter will be the WMFT-O. The long-term results will be assessed prospectively by postal follow-up. All patients will receive conventional occupational and physical therapy. The intervention group will receive additional robot-assisted training using the Armeo®Spring robot for 3 weeks.

**Discussion:**

This study protocol describes a phase II, randomised, controlled, single-blind, multicentre intervention study. The results will guide and possibly improve methods of rehabilitation after proximal humeral fracture.

**Trial registration:**

Clinicaltrials.gov, NCT03100201. Registered on 28 March 2017.

**Electronic supplementary material:**

The online version of this article (doi:10.1186/s13063-017-2274-z) contains supplementary material, which is available to authorized users.

## Background

The number of upper arm fractures is increasing in the aging workforce (52–66 years). The risk for proximal humeral fractures (PHFs) increases with age, starting at around the age of 45 years [1]. In 2008 approximately 370,000 emergency department (ED) visits occurred as a result of humeral fractures in the United States. Of these around 50% were due to PHF (184,300 ED visits), with double the number in females compared with males. In the age group 35–64 years, approximately 57,500 ED visits were recorded. About 275,000 ED visits due to PHF are predicted in 2030 in the United States. A similar trend in numbers is expected in Europe [1].

This relevant number in fractures of the upper extremity already places a high demand on surgical treatment and subsequent rehabilitation [2]. Currently, the existing physiotherapy and occupational therapy concepts are based on expert opinion. No robust evidence-based consensus exists for rehabilitation approaches after PHF [3, 4], which is somewhat surprising. Worldwide no randomised controlled trials (RCTs) have been published comparing rehabilitation protocols for PHFs. Thus, the optimal content, frequency, duration and intensity of rehabilitation after shoulder injuries remain unclear. Not surprisingly, authors of a recent systematic literature review found considerable variation and heterogeneity in rehabilitative treatment after PHF [4]. Researchers in several observational studies have criticized the inadequacy of currently available rehabilitation protocols for PHFs. The functional recovery of the fractured upper extremity was found to be disappointing in a German study [5]. One consistent problem is the long immobilisation of the affected arm of up to 6 weeks [6]. This leads to loss of muscle strength and results in loss of flexibility of the adjacent joints. A shorter time to recovery would be a prerequisite for an improved outcome after PHF [4].

In a pilot safety and feasibility study by our group, robot-assisted training using the Armeo®Spring device (Hocoma, Volketswil, Switzerland), which was originally designed for stroke rehabilitation [7], was shown to be safe and highly acceptable even among older patients. The pre-post measurements indicated a potential improvement in muscle strength, flexibility and motor control [8]. Assistive arm support was used to reduce partial loading of the affected arm and increase the movement request at an early stage after surgery. Thus, robot-assisted training could be a valuable option in orthopaedic fracture rehabilitation. However, evidence for effectiveness so far is confined mainly to the field of neurology, particularly in stroke patients. Literature on fracture rehabilitation using robot-assisted training is extremely scarce. Besides our pilot study, Padilla-Castenada et al. [9] evaluated the use of robot-assisted training after forearm and elbow fracture. They showed that the duration and number of repetitions of exercises can be increased by active assistive training.

Although preliminary, the promising findings of these pilot studies remain to be confirmed in an RCT. Hence, the aim of this study is to test whether additive robot-assisted training in patients with PHF using the Armeo®Spring device is superior to conventional occupational and physical therapy alone.

## Methods/design

### Study design

A single-blind, multicentre intervention RCT will be conducted. Robot-assisted training using the Armeo®Spring device added to conventional occupational and physical therapy will be compared with a control group receiving only conventional occupational and physical therapy.

### Randomisation

Participants will be randomised into one of two arms via block randomisation in each of the three centres, according to a predefined allocation sequence, after assessing inclusion and exclusion criteria. A randomisation list for each centre was created using the Internet-based Sealed Envelope software (https://sealedenvelope.com/; Sealed Envelope, London, UK). Assignment to the intervention and control groups will be performed by study nurses in each centre who will be blinded to interventions; unblinding will not be permissible. Anonymised data will be entered into a central database (Research Electronic Data Capture [REDCap], with data entry in agreement with the International Council for Harmonisation of Technical Requirements for Pharmaceuticals for Human Use standards for good clinical practice, see also SPIRIT procedure in supplementary material; Additional file 1: SPIRIT checklist and Additional file 2: Schedule of enrolment, interventions, and assessments) at the coordinating centre.

Participants will undergo clinical and quantitative assessments at one of the three sites: Robert-Bosch-Hospital Stuttgart, BG Trauma Centre Murnau or BG Trauma Centre Ludwigshafen. These three sites were chosen as comparators because they are the three largest clinical sites in Germany that treat PFH, do research or cooperate with an institute that conducts research, and possess Armeo®Spring devices. All procedures have been approved by the ethics committee of the University of Tübingen (381/2015BO1) and the regional medical association of Rheinland-Pfalz (837.519.15) and are in accord with the Declaration of Helsinki. Informed consent will be obtained from all participants (Additional file 3: Consent form). All participants will be insured. No data monitoring committee was consulted.

### Sample size

Adults in the working population aged between 35 and 66 years will be recruited at all three sites. In a pilot study [8], our group was able to measure an improvement in function with the Disabilities of the Arm, Shoulder and Hand Outcome Measure (DASH) score (median 47 [mean 46 ± 20 SD] to median 34 [mean 32 ± 15 SD]). As a result of a power analysis based on these results, 26 patients per group will be required to achieve 80% power at a significance level of α = 0.05. With an expected drop-out rate of 10%, a total of 60 patients should be recruited, comprising 20 patients at each of the 3 sites.

Inclusion criteria for both groups will be surgical treatment of the shoulder joint after upper arm fracture classified as AO Foundation/Association for the Study of Internal Fixation (Arbeitsgemeinschaft Osteosynthese; AO) type 11 [10]. Participants will be included between the fourth and seventh weeks after surgery. The participant population will be stratified by fracture location (subcapital/capital) and handedness.

Exclusion criteria will be determined during baseline assessment. Participants with limited cognition as defined by a score < 10 points on the Short Orientation-Memory-Concentration Test (SOMC), inadequate level of pain during movement of the affected shoulder joint (pain score > 5 on a pain visual analogue scale [VAS]), strongly limited vision or hearing, heart failure (New York Heart Association stage III-IV), chronic obstructive pulmonary disease with Global Initiative for Chronic Obstructive Lung Disease (GOLD) stage III-IV, walking speed < 0.8 m/second, isolated tuberculum majus fracture of the humerus (AO 11, A1), or fractures with involvement of the glenoid cavity, as well as double fractures or injury of the plexus or the axillary nerve, will be excluded. All participants will give their written informed consent to the study administrators at each centre prior to the clinical baseline assessment.

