**Fig. 1 Fig1:**
[figure not shown]
Plan of assessment and intervention procedures. *DASH* Disabilities of the Arm, Shoulder and Hand Outcome Measure, *ROM* Range of motion, *WMFT-O* Wolf Motor Function Test–Orthopaedic version

Clinical data such as sex, age, body mass index, handedness, date and type of fracture, and date of surgical treatment will be recorded. Furthermore, the participant’s occupation before and after the accident as well as the number of days between the accident and the return to work will be recorded. If the participant will not be able to return to work after the accident, the reason for being incapacitated will be assessed.

The SOMC is an assessment of cognitive impairment and will be applied in this study. It can differentiate between mild, moderate and severe cognitive deficits. The SOMC was derived from the longer Blessed scale [11] to enable it to be performed by a non-physician. The SOMC score highly correlates (*r* = 0.92) with the full scale and is nearly as sensitive as the longer version. Any error score of 0–6 is within normal cognitive limits [12].

In this study the potential pain score in the shoulder during motion will be assessed by the patient and then documented by the therapist as a numerical value. Therefore, a VAS will be used, which was proven to be a valid method for determining pain in clinical routine [13]. As an assessment of overall motor function, the comfortable gait speed over a distance of 10 m will be assessed. The walking course will consist of a total of 14 m, 2 m for acceleration, 10 m for the speed measurement and 2 m for slowing down and stopping. The participants will be directed to walk at their own comfortable pace [14].

The flexibility (range of motion [ROM]) of the shoulder is measured using a goniometer according to the AO neutral-0 method in pain-free range. The maximum angle in elevation, retroversion, abduction and adduction as well as external rotation will be measured. The maximal grip strength will be assessed three times for both hands using a dynamometer (JAMAR Technologies/MSD, Londerzeel, Belgium) according to the American Society of Hand Therapists [15] guideline. The average of three measurements will be calculated for both hands.

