### Intervention

Both the intervention group and the control group received physical and occupational therapy for a period of 3 weeks; concomitant interventions were not restricted. The additional robot-assisted therapy commenced as early as 4 weeks after surgery and not later than 7 weeks after surgery. There are no evidence-based guidelines or requirements on the content, duration or intensity of rehabilitation after shoulder injuries. Typically the therapeutic content consists of exercises for stabilisation and mobilisation of the shoulder and the surrounding joints, as well as muscle strengthening (three to six times per week for 25–30 minutes). The obtained conventional physical and occupational therapy will be documented but not influenced. The frequency and duration of individual training schedules, as well as adverse events, will be recorded in a protocol. Serious adverse events will be treated as criteria for discontinuing the interventions.

The intervention group received robot-assisted training in addition to the protocol intervention. The robot-assisted training will be performed using the clinically evaluated Armeo®Spring medical device. By means of sensory orthosis, arm movements will be supported and transmitted to a computer system and visually shown on a screen. Furthermore, audio feedback elements and augmented performance feedback will be used for guidance. The Armeo®Spring device encourages patients with motivating game-like exercises in an inspiring virtual environment. The sensor-based computer system calculates game kinetics for 3D animation of arm functions, including grasping and goal-orientated functional reaching, as well as object manipulation (e.g., throwing a Frisbee). The mechanism to support the weight of the arm will be increased or decreased gradually to adapt to the ability of the user. Thus, the participant will have the ability to perform targeted and controlled movements in accordance with medical safety standards, including the movement limit as suggested by the operating physician.

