### Statistics

The centre and the number of treatment units will be regarded as possible covariates for the primary outcome. All data assessed will be described descriptively (mean, SD, 95% CI and median for metric variables; frequency and percentile for categorical variables). After checking the data for normal distribution by comparing the distribution histograms and Shapiro-Wilk test, the group comparison will be carried out with the *t* test or the rank-based Wilcoxon test. For the primary outcome analysis of covariance with study centre, number of therapy units (to take account of the training inhomogeneity) and injury severity (to take account of the patient’s homogeneity) as covariates will be performed. The secondary outcome (WMFT) will be analysed to generate study hypotheses using the methods described above. Inferential statistics will follow an intention-to-treat approach with mean imputation or regression imputation for all randomised patients with incomplete datasets if deemed necessary. Per-protocol analysis will be performed for evaluation of the efficacy of the intervention in patients with complete datasets and without protocol violations.

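### Time from surgery to baseline varies by 3 to 4 weeks and can be derived, but is not a primary-model covariate; prespecifying it is a cheap safeguard with a small, uncertain gain in precision

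*Protocol article*

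**What the plan says.** On entry, the Sample size section of the protocol article says: "Participants will be included between the fourth and seventh weeks after surgery". The Intervention section says the robot therapy "commenced as early as 4 weeks after surgery and not later than 7 weeks after surgery". The robot programme lasts 3 weeks. Follow-up 1 falls 3 to 5 weeks after baseline (Clinical assessment).

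On data, the clinical record includes the following: "date and type of fracture, and date of surgical treatment will be recorded". The interval from surgery to baseline is therefore available without further collection.

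On balancing, participants are "randomised into one of two arms via block randomisation in each of the three centres" (Randomisation). The Sample size section adds: "The participant population will be stratified by fracture location (subcapital/capital) and handedness". Time since surgery appears in neither place.

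On analysis, the Statistics section specifies a covariance model for the primary outcome. It names the adjustment terms as follows: "study centre, number of therapy units (to take account of the training inhomogeneity) and injury severity (to take account of the patient’s homogeneity) as covariates". Neither time since surgery nor baseline DASH is on that list.

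**The concern.** Function after a surgically treated humeral fracture can be expected to change over the weeks in which patients enter. If so, someone entering in week 4 and someone entering in week 7 have different expected DASH scores, whatever their treatment. With follow-up 1 at 3 to 5 weeks after baseline, the score may be taken anywhere from about week 7 (4 + 3) to week 12 (7 + 5) after surgery.

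The Statistics section commits to a covariate list and gives reasons for two of its entries, one of them being differences between patients. Injury severity is the only covariate listed for that purpose, and it does not measure how far recovery has progressed. Baseline DASH, which would carry part of that information, is not listed. The possible loss is some precision, plus a chance difference in entry time between two small arms that the model would not correct.

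**Working it through.** **Inputs from the article.** Pilot DASH means 46 and 32 (difference 14), SDs 20 and 15; 80% power, α = 0.05, 26 per group; drop-out 10%, total 60; entry in weeks 4 to 7.

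**Assumptions, because the article gives no figure.** Two-sided test; entry uniform over a window of width w = 3 weeks (end of week 4 to end of week 7) or w = 4 weeks (all of weeks 4 to 7); linear DASH recovery of b = 1 to 5 points per week, unrelated to treatment.

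**1. The planned sample size.** Pooled SD = √((20² + 15²)/2) = √312.5 = 17.68. Normal approximation: n = 2 × (1.960 + 0.842)² × 312.5/14² = 25.03, rounded up to 26. The t-based solution is 26.02, and power at 26 is 0.7996. Allowing for drop-out, 52/0.90 = 57.8, so 58; the plan takes 60, or 20 per site. The stated figure reproduces and does not depend on time since surgery. (A one-sided test with SD 20 also gives 26, so the figure does not settle sidedness.)

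**2. Variance explained by entry time.** SD of entry time = w/√12 = 0.87 weeks (w = 3) or 1.15 weeks (w = 4). R² = (b × SD)²/312.5.

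**3. Chance imbalance between arms.** The SD of the difference in mean entry time is (w/√12) × √(2/26) = 0.24 or 0.32 weeks; multiplied by b it is in DASH points.

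**4. Power with the covariate, 26 per group.** Residual SD = 17.68 × √(1 − R²). To charge the covariate fully, use 49 instead of 50 degrees of freedom and multiply the variance of the treatment difference by 1 + 1/(2 × 26 − 4) = 1.021, the expected cost of estimating one slope.

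| w (weeks) | b (points/week) | R² | Imbalance SD (DASH points) | Power, no charge | Power, fully charged |
|---|---|---|---|---|---|
| 3 | 1 | 0.002 | 0.24 | 0.801 | 0.792 |
| 3 | 3 | 0.022 | 0.72 | 0.808 | 0.800 |
| 3 | 5 | 0.060 | 1.20 | 0.823 | 0.815 |
| 4 | 1 | 0.004 | 0.32 | 0.801 | 0.793 |
| 4 | 3 | 0.038 | 0.96 | 0.815 | 0.807 |
| 4 | 5 | 0.107 | 1.60 | 0.842 | 0.834 |

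Against 0.7996 without the covariate, the fully charged change runs from 0.792 − 0.800 = −0.8 power points to 0.834 − 0.800 = +3.4 or 3.5. Break-even lies at R² of about 0.02. Before the charge, the required number per group falls from 26.0 to 24.5 at most (w = 3) or 23.4 at most (w = 4).

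**5. Bias and type I error without the covariate.** In 40,000 simulated trials of 26 per group under no treatment effect (w = 3; b = 0, 2 and 5), the unadjusted comparison rejected in 5.0% to 5.1%, and the mean difference between arms was within 0.03 points of zero.

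**The case against.** The strongest case against is that randomisation already deals with this. The entry criteria apply to both groups, patients are allocated in blocks within centre after eligibility is checked, and a concurrent control group receives the same conventional therapy. Recovery stage is balanced in expectation, and chance imbalance is already reflected in the standard error. This stands. A reader might infer that the trial compares patients at different stages of recovery, or that natural recovery is the main rival explanation for a DASH difference. The design does not support either; that would be true of an uncontrolled pre-post study such as the pilot.

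A reader might also infer that the window straddles the end of immobilisation, from the Background: "One consistent problem is the long immobilisation of the affected arm of up to 6 weeks". That sentence describes a general problem with care and cites literature. It does not describe this trial's regimen, and nothing in the article says that early entrants are still immobilised and late ones are not.

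The upper slope is generous too. A rate near 4.7 points per week comes from dividing the pilot's 14-point change by an assumed 3 weeks. That treats the whole change in robot-trained patients as natural recovery, and the article does not give the pilot's duration.

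Finally, age, sex, pain and range of motion are also recorded and unlisted. With about 52 evaluable patients a short covariate list is defensible, and the Statistics section already promises a description of all assessed data. This is fair: entry time is not uniquely necessary. What the objection does not remove is that the interval is a true baseline variable whose wide range the entry rule itself creates, and that no listed covariate tracks it.

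**Conclusion.** The point holds as a low-cost improvement; it is not a flaw that threatens validity. Time from surgery to baseline varies by 3 to 4 weeks, can be derived from recorded dates, and is missing from the named primary covariates. The omission produces no expected bias and no excess type I error. Its possible cost is limited to some precision and an uncorrected chance imbalance with an SD of about 0.2 to 1.6 DASH points, at most about 11% of the planned 14 (1.6/14).

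The gain from adjusting is not certain. It ranges from a loss of less than 1 power point if recovery is slow to a gain of about 3.5 points if recovery is steep and the window is 4 weeks wide. The result rests on the assumed slope, linearity and uniform entry, none of which the article supplies. If baseline DASH were also in the model, it would absorb part of this gain.

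Two features of the same covariate list weigh more and are not cured here: baseline DASH is not listed, and the number of therapy units is measured after randomisation.

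**What to change.** In the Statistics section, prespecify days from surgery to baseline assessment as a continuous baseline covariate in the primary analysis of covariance, ideally alongside baseline DASH, and report its distribution by arm in the baseline table.

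The cost is one line of text and one degree of freedom, worth less than 1 power point in the worst case considered. No new data and no change to entry or treatment are needed. The change should be dated and made before outcome data are examined by arm. The Trial status section reports recruitment at 50%, so at that stage it could still be prespecified. If it were added after the results are known, it would be open to the charge of selective adjustment.

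### The stratification by fracture location and handedness stated under Sample size appears neither in the randomisation description nor in the primary model, and the sections need reconciling

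*Protocol article*

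**What the plan says.** Three sections of the protocol article bear on this.

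- **Sample size**, in the paragraph on inclusion criteria: "The participant population will be stratified by fracture location (subcapital/capital) and handedness".
- **Randomisation**: "Participants will be randomised into one of two arms via block randomisation in each of the three centres, according to a predefined allocation sequence", and "A randomisation list for each centre was created using the Internet-based Sealed Envelope software". No stratum other than centre is named, and the block size is not given.
- **Statistics**: "The centre and the number of treatment units will be regarded as possible covariates for the primary outcome". The primary model is then given as: "For the primary outcome analysis of covariance with study centre, number of therapy units (to take account of the training inhomogeneity) and injury severity". Injury severity is not defined. No analysis stratified by fracture location or handedness, and no subgroup analysis by either, is described.

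The Clinical assessment section lists the baseline data: "Clinical data such as sex, age, body mass index, handedness, date and type of fracture, and date of surgical treatment will be recorded". Both factors can therefore be obtained from data named in the article. The injured side is not in that list, although the list is given as examples only.

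**The concern.** A stratification statement normally tells the reader two things: how allocation was restricted, and which factors the analysis should carry. Here it does neither. The section that defines allocation does not use the two factors, and the section that defines the primary model does not name them.

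What is at stake is limited but real in a trial of 60 patients. A reader may credit the design with a balance on fracture location and handedness that it does not provide. Alternatively, the design may provide that balance while the primary analysis discards the precision it bought. If the question is left open until the data are in, any later decision to adjust for these factors can look data-driven.

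**Working it through.** **The plan's own figure.** The sample size does not depend on this point, but it reproduces. The pilot DASH means of 46 and 32 give a difference of 14. The SDs of 20 and 15 give a pooled SD of √((20² + 15²)/2) = √312.5 = 17.68. For a two-sided α of 0.05 and 80% power, n = 2 × (1.960 + 0.842)² × 312.5/14² ≈ 25.03, rounded up to 26 per group; the t-based solution is 26.02. Pooling the SDs and testing two-sided are my reading, since the article states neither. For dropout, 52/0.9 = 57.8, so 58 patients, and 60 is 20 at each of 3 sites.

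**The sections side by side.**

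| Factor | Sample size | Randomisation | Primary ANCOVA |
|---|---|---|---|
| Centre | not named as stratum | yes | yes |
| Fracture location | yes | not named | not named |
| Handedness | yes | not named | not named |
| Injury severity | no | no | yes, undefined |
| Therapy units | no | no | yes |

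**Branch A: lists by centre only.** There are 3 lists of 20 patients. The only restriction on allocation is centre, and centre is in the model. The other two factors are left to chance:

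- With 30 per arm and an assumed 50/50 split on location, the SD of the between-arm difference in share is √(2 × 0.25/30) = 0.129, about 13 percentage points.
- In a simulation of 60 patients with centre-only lists, an assumed block size of 4 and an assumed prevalence of 30% to 50%, the arms differed by 20 points or more on a given binary factor in about 12% to 15% of trials.

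This is ordinary chance imbalance. It does not bias the comparison in expectation.

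**Branch B: lists by centre, location and handedness.** The number of strata is 3 × 2 × 2 = 12, averaging 60/12 = 5 patients, or 20/4 = 5 per cell within a site.

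- *Block filling* depends on the unstated block size. With 5 patients in a stratum, blocks of 2 give two complete and one part-filled, blocks of 4 give one of each, and blocks of 6 give none complete. In simulation, the arm totals ended 6 or more apart in about 3–4%, 10–12% and 17–19% of trials for blocks of 2, 4 and 6.
- *Standard error.* If the omitted factors explain a share R² of the DASH variance left after the other covariates, and allocation is well balanced on them, leaving them out inflates the standard error by about 1/√(1 − R²). The documents give no R². Assumed values of 0, 0.10 and 0.20 give factors of 1.00, 1.05 and 1.12. These only illustrate the formula: sparse, part-filled strata would weaken the balance it requires, and overlap between injury severity and location would lower R².

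**Degrees of freedom for the fix.** With 60 × 0.9 = 54 evaluable patients, a model with intercept, arm, centre (2), therapy units (1) and injury severity (1, if entered as one linear term) uses 6 parameters and leaves 48 residual degrees of freedom. Two binary covariates bring that to 46.

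**The case against.** The strongest reply is that this is a wording inconsistency in a condensed article. The sentence sits among the eligibility criteria and mentions neither randomisation nor balance between arms, so it could refer to description or analysis. The article does not say the lists use centre alone, and strata within a centre's list are not expressly excluded. Injury severity may overlap with fracture type, leaving only handedness clearly absent from the model.

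Much of this stands, and it rules out several stronger readings that a reader might infer:

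- *That a claimed balance is false.* The article does not claim balance, and how the lists were built is inferred from the absence of any other factor.
- *That analysis and allocation fail to match whichever way the lists were built.* Under centre-only lists they do match, because centre is in the model.
- *That a specific inflation of the standard error is established, or that most blocks would be incomplete.* Both rest on figures the documents do not give. Omitting true strata usually makes the analysis conservative, not prone to false positives.
- *That handedness is the wrong factor.* It may be shorthand for whether the dominant arm is injured, and the article gives no basis for deciding.

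The reply does not remove the mismatch. If stratified description or analysis was meant, the Statistics section does not provide it. Nor is this a detail left to a fuller document: the article makes a positive statement and gives a specific covariate list that does not reflect it.

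**Conclusion.** The point holds as an inconsistency between three sections, together with a cheap improvement to the primary analysis. The stated stratification is found in neither the allocation as described nor the model as specified. Under centre-only lists the cost is a misleading description and unadjusted chance imbalance, with no bias in expectation. Under twelve-stratum lists the cost is a standard error that tends to be conservative, by an amount that cannot be fixed from the documents. The sample size is unaffected. The mismatch itself rests on the text alone; every figure for imbalance, block filling or standard error rests on assumed prevalence, block size or explained variance.

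**What to change.** 1. State which factors the existing randomisation lists use and correct the sentence under Sample size to agree. Do not regenerate the lists: the Trial status section puts recruitment at 50%.
2. Prespecify fracture location (subcapital or capital) and handedness as baseline covariates in the primary ANCOVA alongside centre. If the injured side is recorded, dominant arm affected (yes/no) may replace handedness.
3. Define injury severity and say how it relates to fracture location, so that the same information is not entered twice under two names.

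This takes a clarification of the protocol and matching analysis-plan wording, settled before outcomes are analysed. It needs no extra patients and costs about two degrees of freedom. The downside is little gain in precision if handedness is weakly prognostic.
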